### 2.5. Ethics

The study will be carried out in accordance with the principles of the Declaration of Helsinki. Approval for the entire study protocol was obtained by the principal study investigator (PSI) from the Bioethics Committee of the Medical University of Lodz (Bioethics Committee resolution no. RNN/274/25/KE, dated 18 November 2025).

All participants will be provided with written information detailing the study objectives and procedures. Enrollment will occur only after eligibility criteria are met and written informed consent is obtained. Participants will be informed of their right to withdraw from the study at any time without any adverse consequences. Participation in the study involves minimal risk, mainly related to blood sampling such as transient discomfort, bruising, or rarely fainting.

### 2.6. Statistical Analysis

All analyses will be exploratory and hypothesis-generating. Continuous variables will be summarized using means and standard deviations or medians and interquartile ranges, as appropriate, and categorical variables as counts and percentages. Markedly skewed fatty acid variables may be transformed. Fatty acid measures will be standardized to facilitate comparison of effect estimates. Results will be reported with 95% confidence intervals, and *p*-values will be interpreted in the context of the pilot nature of the study. The primary endpoint will be the change in BDI-II total score from baseline to week 6. Associations between individual baseline fatty acids and depressive symptom trajectories will be examined using separate linear mixed-effects models estimated with restricted maximum likelihood. Repeated BDI-II scores obtained at baseline and at weeks 3, 6, and 12 will constitute the dependent variable. Models will include time, the standardized fatty acid measure, the fatty acid-by-time interaction, age, sex, and antidepressant class as fixed effects, with a participant-specific random intercept. The prespecified primary contrast will represent the association between the baseline fatty acid measure and change in BDI-II score from baseline to week 6. Fatty acids will be analyzed individually rather than entered simultaneously into a single conventional multivariable model.

Antidepressant class will initially be categorized as selective serotonin reuptake inhibitor, serotonin–norepinephrine reuptake inhibitor, or other. Categories may be combined if their sizes do not permit reliable estimation. The robustness of the primary findings will be examined in sensitivity models additionally accounting for relevant dietary, metabolic, lifestyle, and treatment-related factors. These may include fish and seafood intake, a plant- and fiber-rich food index, body mass index or waist circumference, physical activity, smoking, alcohol consumption, comorbidities, concomitant medications, psychotherapy, adherence, hospitalization status, and treatment modifications. Because of the limited sample size, these variables will not all be included simultaneously in a single model. Secondary binary outcomes at week 6 will include treatment response, remission, and minimal clinically important improvement. Their associations with individual fatty acids will be examined using separate exploratory logistic regression models with a limited number of prespecified covariates. Penalized likelihood estimation may be used in the event of complete or quasi-complete separation. 

Longitudinal changes in DASS-42 subscales and WHOQOL-BREF domain scores will be examined using analogous mixed-effects models. Baseline relationships between fatty acid measures and psychometric variables will be assessed using Pearson or Spearman correlation coefficients, as appropriate. Principal component analysis will be applied to standardized erythrocyte fatty acid variables to identify broader fatty acid patterns and reduce dimensionality. The number of retained components will be determined using parallel analysis and inspection of the scree plot. Component scores will be evaluated in exploratory models analogous to those used for individual fatty acids. PCA will not be applied to the three serum SCFAs. The Benjamini–Hochberg false discovery rate procedure will be used to account for multiple testing involving individual fatty acids. Correction will be applied separately to the primary family of analyses involving the week 6 BDI-II outcome and to each secondary outcome family. Both unadjusted *p*-values and false-discovery-rate-adjusted *q*-values will be reported. Missing follow-up data will be minimized through regular contact with participants and electronic questionnaires requiring completion of all items. The timing and reasons for missed assessments and withdrawal will be recorded. Mixed-effects models will use all available repeated observations and will provide valid estimates under the missing-at-random assumption. Missingness patterns will be examined descriptively, and the potential impact of departures from this assumption will be evaluated in sensitivity analyses if the amount of missing data permits. Missing baseline fatty acid measurements will not be imputed. The study is not designed to establish clinical cut-offs or validate a clinical prediction tool. If an exploratory combined prediction model is developed, its apparent performance and optimism will be assessed using bootstrap resampling. Such findings will require external validation in future adequately powered studies.

Analyses will be performed using Statistica 13.3 and the R software 4.6.1.

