### 1.2. Aims and Hypotheses

Our aims are the following:

-The primary aim of the current pilot study is to investigate the association between baseline fatty acid profiles and the magnitude of antidepressant treatment response and to generate preliminary effect size estimates to inform the design of a future adequately powered study examining the predictive utility of fatty acid biomarkers in depression.-The secondary objective is to investigate the association between the erythrocyte membrane and serum fatty acid profiles and the clinical presentation of depressive disorders, encompassing the severity of depressive symptoms, anxiety symptoms, and stress-related symptoms, as assessed by the Depression, Anxiety and Stress Scales (DASS-42) and the Beck Depression Inventory-II (BDI-II).

We assume that the profile of long-, medium-, and short-chain fatty acids in blood may be associated with the course and clinical picture of depression. The main confounding factors are hypothesized to be diet, physical activity, and somatic comorbidities, with their treatment.

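### Age, sex and antidepressant class enter the primary mixed model only as main effects, so they leave the baseline-to-week-6 contrast effectively unadjusted

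*Protocol article*

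**What the plan says.** Section 2.6 (Statistical Analysis) specifies the primary model closely. On the outcome: "Repeated BDI-II scores obtained at baseline and at weeks 3, 6, and 12 will constitute the dependent variable". On the fixed effects: "Models will include time, the standardized fatty acid measure, the fatty acid-by-time interaction, age, sex, and antidepressant class as fixed effects". The only random effect is an intercept for each person. On the target: "The prespecified primary contrast will represent the association between the baseline fatty acid measure and change in BDI-II score from baseline to week 6". The fatty acid-by-time term is the only interaction listed, and no covariate-by-time term appears anywhere in the article.

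Robustness is to be checked in "sensitivity models additionally accounting for relevant dietary, metabolic, lifestyle, and treatment-related factors". The candidates include baseline-type variables (dietary intake, BMI or waist, physical activity, smoking) and variables that can change during follow-up (adherence, psychotherapy, treatment modifications). How they enter the model is not said.

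The same model form is carried over: "Longitudinal changes in DASS-42 subscales and WHOQOL-BREF domain scores will be examined using analogous mixed-effects models". Principal component scores are handled likewise.

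Section 1.2 shows that adjustment matters to the authors: "The main confounding factors are hypothesized to be diet, physical activity, and somatic comorbidities, with their treatment".

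**The concern.** Listing age, sex and class as fixed effects reads as adjustment of the primary result. But the primary contrast is a within-person change, and each of these covariates gets one coefficient that applies to every visit. Such a term adjusts the level of BDI-II, not its change. A factor related both to the fatty acid and to the rate of improvement is left in the estimate.

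The stated aim of the pilot (sections 1.2, 2.2 and the Discussion) is to supply effect-size estimates for a larger study. An estimate labelled as adjusted but effectively unadjusted would go straight into that calculation. If the sensitivity models copy the primary form for baseline covariates, a near-identical result would be read as robustness when it is a property of the algebra.

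**Working it through.** **The plan's own figure.** The only design figure is 30 expected responders among 60 (60 × 0.50 = 30, section 2.2). It reproduces, and nothing below depends on it.

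**Algebra.** For participant *i* at visit *t*, with fatty acid *x* and a time-fixed covariate *z*, the stated model is

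*y_it* = α_t + β_t *x_i* + γ *z_i* + *u_i* + *e_it*.

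The change to week 6 is

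*y_i6* − *y_i0* = (α_6 − α_0) + (β_6 − β_0) *x_i* + (*e_i6* − *e_i0*).

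Both γ*z_i* and the random intercept drop out. With all four visits observed, the estimate of β_6 − β_0 does not involve *z*. Its standard error rests on the within-person residual variance, which *z* does not touch either. Adjustment requires γ to differ by visit. This is true whether time is categorical or linear.

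**If the covariate does act on change.** With *x* and *z* standardised, correlation *r*, and *z* changing the week 6 improvement by *b* points per SD, the bias is *r* × *b*. Neither quantity is in the documents. Assuming *r* = 0.4 and *b* = 3 gives 0.4 × 3 = 1.2 BDI-II points per SD of fatty acid. Halving one input gives 0.6, halving both gives 0.3, and if either is zero there is no bias.

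**Simulation 1: several covariates.** Assumptions: N = 60; visits at weeks 0, 3, 6 and 12; random-intercept SD 7; residual SD 6; age, sex and BMI related to both the fatty acid and BDI-II change; true conditional fatty acid effect on week 6 change zero. REML random-intercept fits, 200 datasets. The first two columns give the mean fatty acid × week 6 estimate; the last two give the largest difference from the no-covariate fit.

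| Model | Complete | 20% missing per follow-up visit | Max diff., complete | Max diff., 20% missing |
|---|---|---|---|---|
| No covariates | 3.581 | 3.683 | – | – |
| Age, sex, class as main effects (as specified) | 3.581 | 3.680 | 0.0000 | 0.22 |
| The same plus BMI as main effect | 3.581 | 3.679 | 0.0000 | 0.31 |
| Age, sex, class × time | 1.789 | 1.866 | 5.20 | 5.82 |
| The same plus BMI × time | 0.054 | 0.027 | 7.69 | 10.38 |
| As specified plus a visit-specific covariate | 3.596 | 3.671 | 1.15 | 1.14 |

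Only the interaction models approach the true value of zero. In the last row the visit-specific covariate had no effect on the outcome, so the mean barely moves. The row shows only that the exact invariance is gone.

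In one illustrative complete dataset the first three models all gave 5.897881 (SE 1.3102). Age, sex and class × time raised the SE to 1.7036 (1.7036 / 1.3102 = 1.30), and adding BMI × time raised it to 2.1695 (2.1695 / 1.3102 = 1.66).

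**Simulation 2: one covariate.** *r* = 0.4, *b* = 3, no true fatty acid effect, the same SDs, 300 complete datasets. The mean estimate was 1.18 without the covariate, 1.18 with its main effect (largest difference about 1e-14) and 0.04 with covariate × time. The mean SE went from 1.14 to 1.22 (1.22 / 1.14 = 1.07). Rejection at nominal 5% was 19% against 7%, with Monte Carlo error of about 2 points. A separate run of 4,000 change-score regressions with the same *r* and *b* gave 12.5% against 4.8%. The error rate thus depends on the assumed SDs and the fitted model.

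**The case against.** A reader might infer that no planned sensitivity analysis could reveal confounding. The documents do not support that. Section 2.6 leaves the form of those models open, which an article may do. Several listed covariates can vary over follow-up, and section 2.1 has treatment changes and psychotherapy reported at each assessment; entered as visit-specific values, they would move the contrast even as main effects. The planned exclusion of participants with major treatment modifications before week 6 changes the sample and is also untouched by this problem.

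A reader might also infer that all week 6 evidence is unadjusted. That is not so: covariates work as usual in the logistic models for response, remission and minimal clinically important improvement. Nor can a particular bias or false-positive rate be attributed to this plan, because every input to those figures is assumed.

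The remaining defence is that this is an exploratory pilot without a power claim, and that an unadjusted association with change is a legitimate quantity when the interest is prediction. That lowers the stakes. It does not answer the point: the protocol names confounders, lists adjustment terms, and wants effect sizes to plan from. If an unadjusted estimate is intended, section 2.6 should say so.

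**Conclusion.** The concern holds for the primary model as written. Age, sex and antidepressant class have no effect on the primary contrast with complete data and a negligible one with missing visits (at most 0.22 points in 200 simulated datasets with 20% missing, against a mean estimate of about 3.7). The DASS-42, WHOQOL-BREF and component-score models inherit this. For the sensitivity models the conclusion is conditional: they would be uninformative about baseline-only covariates if those are added as main effects.

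The exact cancellation rests only on the stated specification and complete data. The amount of confounding left in the estimate, from none to the several points seen in the harshest scenario above, rests on correlations, effects and SDs that the documents do not give.

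**What to change.** In section 2.6:

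- Add covariate-by-time terms for age, sex and antidepressant class to the primary model.
- Do the same for each baseline covariate in a sensitivity model, one or a few at a time given n = 60.
- State that covariates which change during follow-up enter as visit-specific values.
- Apply the same form to the DASS-42, WHOQOL-BREF and component-score models.

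An alternative is to model BDI-II at weeks 3, 6 and 12 with baseline BDI-II as a covariate and covariate-by-visit terms. It is not equivalent: it conditions on baseline severity, which the protocol supposes may be related to fatty acids, and so changes the estimand. The choice should be made before analysis.

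The cost is wording, with no new data, visits or participants. With time categorical and three class levels, the primary model gains up to 12 fixed-effect parameters (1 for age + 1 for sex + 2 for class = 4, times 3 follow-up visits), fewer if classes are merged. Precision falls. With one covariate the SE rose by about 5% in one simulated dataset (1.189 to 1.253) and about 7% on average over 300. With several correlated covariates it rose by 30% to 66% in the illustrative dataset. At this sample size that loss is a reason to keep each covariate set short.

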## Abstract

**Background/Objectives**: Despite the availability of multiple pharmacological treatment options, up to one-third of patients with depressive disorders fail to achieve adequate symptom relief following first-line antidepressant therapy, representing a major unmet clinical need. Fatty acids—including short-chain (SCFAs), medium-chain (MCFAs), and long-chain polyunsaturated fatty acids (PUFAs)—are increasingly implicated in depression pathogenesis through neuroinflammation, gut–brain axis signaling, and neurotransmitter metabolism, but their potential as predictors of antidepressant response remains largely unexplored. The primary aim is to evaluate whether baseline fatty acid profiles can predict pharmacological antidepressant treatment efficacy. The secondary objective is to assess the association between blood fatty acid profile and clinical presentation of depressive disorders. **Methods**: Sixty adults diagnosed with depressive disorders (ICD-11) at the initiation of a new antidepressant treatment will be recruited from psychiatric settings. Fasting blood samples collected at baseline will undergo gas chromatographic analysis of fatty acid methyl esters (FAMEs) and GC-MS quantification of SCFAs (acetic, propionic, and butyric acids). Clinical outcomes will be assessed at baseline and at 3, 6, and 12 weeks using the Beck Depression Inventory-II (BDI-II) and the Depression Anxiety Stress Scales (DASS-42). The primary endpoint is the change in BDI-II total score from baseline to week 6. Treatment response, defined as a ≥50% reduction in BDI-II total score at week 6, and remission, defined as a BDI-II score ≤12 at week 6, will be examined as secondary outcomes. Dietary habits, physical activity, quality of life, and anthropometric parameters will be collected as potential confounders. **Discussion**: This study is among the first prospective investigations to comprehensively characterize the circulating fatty acid spectrum as potential predictors of antidepressant outcomes. Findings may support identification of metabolic phenotypes of depression and contribute to personalized treatment strategies.

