The Frequency Questionnaire (FFQ-6) is a dietary assessment tool designed to evaluate habitual food consumption patterns over a specified retrospective period. The questionnaire focuses on the frequency of intake of selected food groups. Participants are asked to report how often they consume specific food items or food categories using predefined frequency options. The FFQ-6 enables estimation of dietary patterns, nutrient intake proxies, and adherence to specific dietary behaviors, including those relevant to lipid and fatty acid intake. The study will use the Polish validated version of the FFQ-6 questionnaire by Niedzwiedzka et al. [33].

Dietary data obtained from the FFQ-6 will be aggregated into predefined food groups for the purpose of statistical adjustment. The following groups will be distinguished: sweets and snacks, dairy and eggs, cereal products, oils, fruits, vegetables and seeds, meat (including fish and its subcategories of processed and unprocessed meat), alcohol, and drinks excluding water. Selected groups will be further subdivided into processed and unprocessed subcategories. For each group, a dietary index will be calculated based on the mean consumption frequency of constituent products. A composite processed food index will additionally be derived from items classified as processed across multiple food categories. These indices will serve as dietary covariates in regression analyses examining fatty acid profiles in relation to clinical outcomes [34].

The International Physical Activity Questionnaire (IPAQ) was developed by an international consortium to provide a standardized measure of physical activity suitable for international and cross-cultural use. A large reliability and validity study conducted across 12 countries (including translation and cultural adaptation procedures) showed acceptable measurement properties [35]. The study will use the Polish version of the IPAQ compiled by Biernat et al., which has been officially translated and registered for use in Poland and enables classification of physical activity into internationally standardized MET-minute categories [36].

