### 2.4. Biological Parameters

Physical examination parameters: weight, body mass index (BMI), and waist circumference (WC).

Anthropometric indicators such as BMI and waist circumference are essential covariates in research examining circulating fatty acid levels.

BMI provides a general estimate of overall adiposity, which influences lipid metabolism, fatty acid storage, and mobilization. Individuals with higher adiposity often present altered profiles of circulating fatty acids due to changes in lipid turnover, insulin sensitivity, and adipose tissue function. Waist circumference, in contrast, is a specific marker of visceral fat accumulation, which is metabolically more active than subcutaneous fat.

Visceral adiposity is strongly associated with disruptions in lipid homeostasis, increased lipolysis, and elevated flux of free fatty acids into the bloodstream. Consequently, it may significantly modify the concentrations of fatty acids measured in plasma or serum [37].

Blood samples will be collected in the morning after an overnight fast by qualified medical personnel. CRP and complete blood count will be assessed in all participants using blood collected during the baseline visit. The neutrophil-to-lymphocyte ratio will be calculated as the absolute neutrophil count divided by the absolute lymphocyte count.

To obtain serum, blood will be collected into tubes without anticoagulants or preservatives and kept in an upright position at room temperature for 30–45 min to allow for clot formation. The samples will then be centrifuged for approximately 10–15 min at 3000× *g*. After centrifugation, the serum will be carefully aspirated and transferred into patient code-labeled cryovials.

To obtain the erythrocyte pellet for FAME analysis, blood will be collected into tubes containing ethylenediaminetetraacetic acid (EDTA) and gently mixed immediately after collection. The samples will then be centrifuged for approximately 10–15 min at 3000× *g*. After centrifugation, the plasma will be carefully aspirated in order to isolate the pellet which will be washed twice with isotonic saline to remove residual proteins and transferred into patient code-labeled cryovials.

Post-centrifugation pellet samples will be frozen and stored in the Biobank.

The samples will be transported on dry ice from the Medical University of Lodz to the collaborating laboratories.

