Regarding personalized antidepressant strategies, we hypothesize that fatty acid profiling could eventually facilitate a ‘match/mismatch’ clinical approach. Identifying a patient with a low baseline EPA:DHA ratio, reduced erythrocyte EPA and DHA levels, an elevated AA/(EPA + DHA) ratio, or depleted SCFA concentrations—potentially in combination with elevated inflammatory markers such as CRP or NLR, and indicators of gut microbiota dysregulation—may indicate an underlying inflammatory or gut-dysbiosis-associated phenotype of depression. In clinical practice, such a biomarker profile could flag a patient likely to respond poorly to a standard monotherapy but who might benefit from targeted adjunctive interventions—such as nutritional or anti-inflammatory strategies—tailored to their metabolic phenotype. Furthermore, by adjusting for dietary intake assessed with the FFQ-6 and anthropometric parameters, this study will provide foundational data on whether fatty acid thresholds need to be personalized based on metabolic characteristics, bringing precision psychiatry closer to routine clinical implementation.

Several limitations of the present study should be acknowledged. First, depressive symptom severity and treatment response will be assessed exclusively using self-reported measures, namely the BDI-II and DASS-42, without the inclusion of clinician-rated scales such as the Hamilton Depression Rating Scale (HAM-D) or the Montgomery–Åsberg Depression Rating Scale (MADRS). This should be considered when interpreting treatment response and remission outcomes.

Second, the study does not include a healthy control group. While the primary objective is to identify predictors of antidepressant treatment response rather than to characterize fatty acid abnormalities relative to a reference population, the absence of controls limits the ability to contextualize baseline fatty acid profiles and to draw conclusions regarding disease-specific alterations in lipid metabolism.

Third, participants will be recruited exclusively from clinical settings. While this approach ensures diagnostic rigor and clinical homogeneity of the study sample, it may limit the generalizability of findings to individuals with depressive disorders who do not seek specialist care or who are managed outside of institutional healthcare settings.

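### The factors the protocol names as main confounders are absent from the primary model, and the open-ended sensitivity models, if built the same way, would not adjust the week 6 change for them

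*Protocol article*

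**What the plan says.** Section 1.2 states: "The main confounding factors are hypothesized to be diet, physical activity, and somatic comorbidities, with their treatment". Section 2.3 says of the food-group indices: "These indices will serve as dietary covariates in regression analyses examining fatty acid profiles in relation to clinical outcomes". The Discussion says that "by adjusting for dietary intake assessed with the FFQ-6 and anthropometric parameters, this study will provide foundational data". Section 2.4 adds a general remark about the field: "Anthropometric indicators such as BMI and waist circumference are essential covariates in research examining circulating fatty acid levels".

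The primary model in section 2.6 is narrower: "Models will include time, the standardized fatty acid measure, the fatty acid-by-time interaction, age, sex, and antidepressant class as fixed effects", with a random intercept per participant. The headline quantity is also fixed: "The prespecified primary contrast will represent the association between the baseline fatty acid measure and change in BDI-II score from baseline to week 6".

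Section 2.6 then commits to testing robustness in sensitivity models that account for dietary, metabolic, lifestyle and treatment-related factors. Their content is left open: "These may include fish and seafood intake, a plant- and fiber-rich food index, body mass index or waist circumference", followed by activity, smoking, alcohol, comorbidities, concomitant medications and others. It explains that the sample is too small to enter all of them together.

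**The concern.** The article says in one place which factors are expected to distort the association and in another specifies a primary model without any of them. The step meant to cover the gap has no minimum set and no stated form for the covariates.

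Two things are at stake. First, section 1.2 makes preliminary effect sizes the product of this pilot, and the Discussion wants to use them to size later cohorts. A slope that partly reflects adiposity or diet would carry into that planning, and false discovery rate correction does not remove bias. Second, if the sensitivity models simply add covariates to the primary structure, they will return nearly the same week 6 estimate. A reader would take that as evidence of robustness when the confounding had not been tested.

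**Working it through.** **The plan's own figure.** The only derived number is the expected split in section 2.2: 60 × 0.50 = 30 responders and 30 non-responders. It reproduces but does not bear on this point. The documents give no correlations, no SD of change and no attrition rate, so the inputs in steps 2 to 4 are assumptions.

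**Step 1: the passages side by side.**

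| Factor | Where it is named | Primary model | Sensitivity models |
|---|---|---|---|
| Diet | 1.2, 2.3, Discussion | absent | optional |
| Physical activity | 1.2 | absent | optional |
| Somatic comorbidities and their treatment | 1.2 | absent | optional |
| BMI or waist | 2.4 (general remark), Discussion | absent | optional |

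**Step 2: possible size of the bias from one omitted factor C.** With standardized variables, bias = r(acid, C) × b(C on change), and SE ≈ 1/√60 = 0.129.

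- Both at 0.1: 0.01, and 0.01/0.129 = 0.08 SE.
- Both at 0.2: 0.04, or 0.31 SE.
- Both at 0.3: 0.09, or 0.70 SE.
- Both at 0.4: 0.16, or 1.24 SE.

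If the SD of BDI-II change were 11 points, this would be 0.01 × 11 = 0.11 to 0.16 × 11 = 1.76 points per SD of acid. With no true effect, the chance of nominal p < 0.05 is Φ(−1.96 − d) + 1 − Φ(1.96 − d), where d is the bias in SE units. It runs from 5.1% (d = 0.08) to about 24% (d = 1.24). This is a rate per affected acid, before any false discovery rate correction.

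**Step 3: whether a main effect would help.** A baseline covariate entered as a main effect adds the same amount to a participant's score at every visit, so it cancels from the week 6 minus baseline difference. With complete data and a random intercept, the acid-by-week-6 contrast does not move.

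A simulation confirms this. Inputs: 60 participants, visits at weeks 0, 3, 6 and 12, time as categories, REML, 150 runs, true acid effect on change of zero, r(acid, C) = 0.4, and C shifting week 6 change by 4 points per SD. The within-participant SD was 6, so the SD of change is √(16 + 2 × 36) = 9.4 and C correlates 4/9.4 = 0.43 with change. That is just above the top of the range in step 2.

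| Model | Slope, complete data | Mean SE | Slope, 15% of follow-up visits missing |
|---|---|---|---|
| No covariates | 1.75 | 1.18 | 1.69 |
| Protocol model (age, sex, class) | 1.75 | 1.18 | 1.69 |
| Protocol model + C as main effect | 1.75 | 1.18 | 1.69 |
| Protocol model + C by time | 0.11 | 1.24 | −0.04 |

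The bias expected by construction is 0.4 × 4 = 1.6. The Monte Carlo error of each mean is about 1.18/√150 = 0.10, so 1.75 agrees with 1.6 and 0.11 with zero. With complete data, the first three models agree to about 10⁻¹⁴ in every run. With missing visits, single runs differ by at most 0.23. Age, sex and class behave the same way: as main effects they barely adjust the primary contrast.

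**Step 4: cost of adjusting.**

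- BMI alone: 1/√(1 − r²) is 1.02 at r = 0.2 and 1.09 at r = 0.4, so the SE rises about 2% to 9%. In the simulation it rose by 1.24/1.18 = 1.05.
- Three to five one-df covariates at 60 participants: √[(df₀/df₁)/(1 − R²)], with df₀ = 54 and R² the share of acid variance explained. Three covariates at R² = 0.1 give √[(54/51)/0.9] = 1.085. Five at R² = 0.3 give √[(54/49)/0.7] = 1.255. A four-factor model lies between, at about 9% to 26%.
- With 30% attrition (n = 42): 1.10 to 1.29.

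These figures ignore any outcome variance the covariates explain, which would offset part of the cost.

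**The case against.** The strongest reply is that this is an exploratory study of association and prediction. A fatty acid that tracks BMI can still predict improvement, so its unadjusted slope is not spurious for that purpose. Diet lies upstream of the exposure, since section 2.4 says erythrocyte composition reflects intake over the preceding 90 to 120 days, and adjusting for it may remove real exposure variance. A sparse primary model with wider sensitivity models is a defensible design, and section 2.6 gives a sample-size reason for it. An article may also leave the exact covariate list to a fuller document.

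Much of this stands. It is a good reason to keep the sparse model as primary and report the adjusted one beside it. It does not answer the rest. Sections 1.2 and 2.3 use the language of confounding and commit to dietary covariates. The sample-size reason rules out entering every variable together, not a small fixed set. And the article does state the primary model's structure, in which main-effect adjustment leaves the contrast where it was.

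A reader might infer four stronger things that the documents do not support:

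- That the adjusted analysis might never be run. Section 2.6 commits to sensitivity models; only their content is open.
- That the primary estimates are confounded. Section 1.2 only hypothesizes it, and the bias may be negligible.
- That section 2.4 requires BMI in the primary model. It is a general remark about circulating fatty acids, and most of this panel is measured in erythrocytes.
- That listing quality of life as a confounder in the Abstract is an analysis error. Section 2.6 does not name it as a covariate, so this is a wording matter.

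**Conclusion.** The point holds as a mismatch between the stated confounders and the stated models, made worse by the way covariates enter. The primary slopes may be confounded by measured factors. How much is unknown: under assumed correlations of 0.1 to 0.4, the range is from negligible to about 1.2 standard errors for one factor at 60 participants. Firmer, because it follows from the model structure, is that covariates added as main effects leave the week 6 contrast unchanged with complete data and nearly so with 15% of follow-up visits missing. Section 2.6 does not say how the sensitivity covariates enter. If they follow the primary model, the check cannot detect confounding of change. The repair should be made before analysis, but nothing here invalidates the design.

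**What to change.** In section 2.6, replace the optional list with one fixed adjusted model run for every acid: BMI or waist, one diet index relevant to that acid, physical activity, and comorbidity. Enter each with a time interaction, or use a week 6 model adjusted for baseline BDI-II. The second option conditions on baseline severity, so choose between them in advance. Name the diet index exactly: the two that section 2.6 mentions are not among the food groups listed in section 2.3.

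Report this model beside the age, sex and class model for the week 6 contrast, and align sections 1.2 and 2.3 and the Discussion with it. Adding BMI or waist by time to the primary model itself is an option. The remaining listed variables can stay as further sensitivity analyses.

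The cost is wording and precision, since collection of all these variables is already planned. Under the assumptions above, the standard error rises roughly 2% to 9% for BMI alone and about 9% to 26% for the four-factor model at 60 participants. That is why the fuller model is co-reported and does not replace the primary.
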